### Study Randomization

Participants will be stratified according to self-reported sedentary time at baseline (high: >8 h/d, medium: 4-8 h/d, and low: <4 h/d) assessed via the International Physical Activity Questionnaire [87]. Participants (n=60) will be randomized 1:1 in REDCap [85], and research staff will text each new participant a unique code (HealthyCells: 0101 and HealthyCells+: 0202) to access assigned app content.

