#### MHBC Intervention: HealthyCells+

In addition to the small financial incentives earned for biochemically verified abstinence, HealthyCells+ intervention participants will earn small incentives for increasing physical activity (ie, daily step count) during their quit attempt. Starting on their scheduled quit date, participants will be rewarded US $0.50 per 1000 steps for every step >4000 daily steps, and they will receive a US $2.50 bonus if they walk at least 6000 steps a day. These criteria were set based on research showing Black adults walk about 4000 steps per day on average [92]. Providing incentives above this threshold will ensure the incentive protocol will not reinforce a sedentary lifestyle, and a bonus for meeting the 6000-step per day goal will reinforce higher levels of daily physical activity and greater positive health benefits [92-100]. Participants will not be incentivized beyond 10,000 steps per day, consistent with previous research showing limited additional health benefits [93,95-100]. Therefore, the maximum amount participants can earn per day for daily steps will be US $5.50 (ie, US $3.00 for 10,000 steps +US $2.50 for step goal bonus), an amount that parallels the amount participants can earn at the fourth week postquit date for daily smoking abstinence.

Participants will self-report their daily step count via an assessment on the app home menu at the end of each day (based on self-reported typical time to bed). This assessment will also ask participants to upload a picture of their step count (captured by the smartwatch; Figure 4). To promote compliance, participants will receive US $1 for each successful photo upload (up to 7 submissions/US $7/wk). Participants will not earn incentives for their self-reported step count total if an image is not uploaded. Consistent with the incentive schedule for smoking cessation, participants will earn these incentives for increasing physical activity starting on the scheduled quit date up to 4 weeks postquit date. Incentives may also be earned during the final 7 days of the intervention period (eighth wk postquit date). To gain the maximum incentives for increasing physical activity (US $255.5), participants must submit all step count photos and take 10,000 steps daily during all eligible assessment weeks (ie, wk 1-4 and the eighth wk postquit date).

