### Analytic Plan

This analytic plan will focus on describing intervention feasibility. Feasibility indicators will include enrollment of all study participants within 12 months (≥5 adults enrolled/mo), retention of at least 75% of the participants at 8 weeks postquit date, achieving 20% smoking abstinence at 8 weeks postquit date (consistent with NRT and behavioral support standards) [104,105], and observing a meaningful 500 to 1500 [106,107] average daily step increase at eighth week postquit date. SAS (version 9.4; SAS Institute) [108] will be used for all statistical analyses, generating descriptive statistics to compare demographics, smoking status, and physical activity levels by treatment group. Group comparisons on participant characteristics and outcomes will use 2-tailed *t* tests for continuous variables and chi-square tests for categorical variables. Given the small sample size and pilot design (N=60), we will report all potential group differences with the α set at *P*<.20, following recommendations for pilot studies [109].

Smoking cessation will be analyzed in two ways: (1) an intention-to-treat analysis with missing data classified as smoking and (2) a completers-only analysis excluding participants with missing data. For physical activity outcomes, specifically the change in average daily step count from the baseline week to the eighth week postquit date, *t* tests will evaluate pre-post differences between groups. Days with <500 steps or <10 hours of watch wear time (indicating nonwear time or recording error) will be excluded. Participants must have at least 4 days of valid step count data to be included in the analyses.

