Exploratory analyses will examine the association between physical activity and smoking cessation success using continuous and categorical approaches, with 6000 steps as the threshold for categorical analyses. Logistic regression analysis will evaluate the impact of average daily step count based on all postquit assessment weeks (5 wk in total) on CO-verified 7-day point prevalence abstinence at 8 weeks postquit date. In addition, participants will be categorized based on achieving a daily average of ≥6000 steps, allowing us to evaluate whether higher activity levels (≥6000 steps) are associated with greater cessation success. Finally, we will explore additional metrics, including the number of consecutive abstinent days and the frequency of meeting daily step goals. The analysis will examine these metrics as continuous and categorical variables to assess their association with smoking cessation rates.

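### With about 9 to 12 abstainers expected, the exploratory logistic regression of abstinence on steps would be better fitted with Firth's penalty, and the 6000-step split reported with counts and a sparse-data method

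*Protocol article*

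**What the plan says.** The exploratory part of the Analytic Plan states: "Logistic regression analysis will evaluate the impact of average daily step count based on all postquit assessment weeks (5 wk in total"), with CO-verified 7-day abstinence at 8 weeks as the outcome. One predictor is named and no covariates are listed. The section also plans a categorical approach, "with 6000 steps as the threshold for categorical analyses", under which "participants will be categorized based on achieving a daily average of ≥6000 steps". No model or test is named for that split. The only test the section names for categorical variables is chi-square, there for group comparisons.

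The scale is fixed elsewhere:
- Study Randomization: "Participants (n=60) will be randomized 1:1 in REDCap".
- Analytic Plan, benchmarks: "achieving 20% smoking abstinence at 8 weeks postquit date" and "retention of at least 75% of the participants at 8 weeks postquit date".
- Analytic Plan, smoking outcome: "an intention-to-treat analysis with missing data classified as smoking", plus a completers-only analysis.
- Analytic Plan, steps: at least 4 valid days are required, and a gain of 500 to 1500 steps is the benchmark.
- HealthyCells+ section: the incentive thresholds rest on "research showing Black adults walk about 4000 steps per day on average".

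No between-person SD of steps and no expected share above 6000 is given.

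**The concern.** The effective size of a logistic regression is set by its rarer outcome, here the abstainers. With around ten of them, maximum likelihood pushes a non-null log odds ratio away from zero on average. For a binary predictor, one empty cell in the 2x2 table leaves no finite estimate at all. The article's targets put the trial in the region where both effects can appear, and the plan names no method that guards against either. At stake is the reported size of the activity-cessation association, and whether the 6000-step comparison yields a usable estimate. Recruitment, retention and the other feasibility results are not affected.

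**Working it through.** The article states no event count, odds ratio or power for this analysis, so there is no planned figure to reproduce.

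**1. Expected abstainers.** 60 × 0.20 = 12 with missing counted as smoking. With 75% retained, 60 × 0.75 = 45 completers, and 45 × 0.20 = 9. The 95% binomial ranges are 6 to 18 and 4 to 14. If the 20% benchmark is met on all 60, completers could instead hold up to 12 of 45 (27%); the article does not say which population the benchmark uses. The 4-valid-day rule can lower N further.

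**2. Continuous steps.** One normally distributed predictor was simulated with 20% abstinent and 5000 data sets per setting. Percentages are the bias of the mean log odds ratio.

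| N | True OR per SD | Maximum likelihood | Firth | SD of ML log OR |
|---|---|---|---|---|
| 60 | 1.5 | +8.5% | +0.3% | 0.39 |
| 60 | 2.0 | +8.4% | −0.4% | 0.43 |
| 45 | 1.5 | +13.7% | +1.8% | 0.49 |
| 45 | 2.0 | +13.0% | +0.3% | 0.54 |

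- Monte Carlo error is about 0.39/√5000 ÷ ln 1.5 = 1.4 percentage points in the first row. Other runs for these settings gave 7 to 11% at N=60 and 12 to 15% at N=45.
- With 12 of 45 abstinent, the maximum-likelihood bias is 10 to 13%.
- At a true OR of 1 there is no bias.
- Non-convergence is essentially nil.
- Root mean squared error is about 9 to 16% lower with Firth.
- On the odds-ratio scale, in a separate run of 6000, a true OR of 2 had a back-transformed mean of 2.13 (N=60) or 2.20 (N=45), and a median of 2.05 or 2.08.

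**3. Share averaging 6000 or more (assumption).** Share = 1 − Φ((6000 − mean)/SD), with an assumed SD.
- Mean 4000 (no gain): 9% at SD 1500, 16% at SD 2000, 21% at SD 2500.
- Mean 4500 to 5500 (the full 500 to 1500 gain in everyone): 23 to 40% at SD 2000, 27 to 42% at SD 2500.
- Gain in HealthyCells+ only, arms averaged: 13 to 23% at SD 1500, 19 to 28% at SD 2000, 24 to 32% at SD 2500. For example, at SD 2000: (15.9 + 22.7)/2 = 19.3 and (15.9 + 40.1)/2 = 28.0.

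**4. The 6000-step split.** Exact binomial enumeration of the 2x2 table, no true association. Expected active-and-abstinent count = N × share × abstinence rate.

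| Share ≥6000 | No finite OR, N=60 (12 events) | No finite OR, N=45 (9 events) | Expected cell count, N=60 / N=45 |
|---|---|---|---|
| 9% | 34% | 46% | 1.1 / 0.8 |
| 16% | 14% | 23% | 1.9 / 1.4 |
| 23% | 6% | 12% | 2.8 / 2.1 |
| 31% | 2% | 6% | 3.7 / 2.8 |

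With 12 of 45 abstinent the N=45 column becomes 37, 14, 6 and 2%. A true association lowers these rates at small shares: at a 10% share, moving from a true OR of 1 to 2 takes them from 30% to 16% (N=60) and from 42% to 27% (N=45).

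**5. Chi-square reading.** The expected active-and-abstinent count is below 5 whenever the share is under 5/12 = 42% (N=60) or 5/9 = 56% (N=45). That covers nearly all the shares in step 3.

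**The case against.** The strongest reply is that the text does not commit to the analysis being faulted. Logistic regression is named for continuous steps only. The 6000-step split could equally be a chi-square comparison, which has no infinite estimate. No estimator is stated anywhere, and an analysis plan that is not shown may already name a penalised fit. The analysis is exploratory, and Sample Size Justification and Strengths and Limitations both disclaim power. The bias in the continuous model is roughly 0.03 to 0.09 on the log scale, against a sampling SD of 0.39 to 0.54. All of this stands and limits the weight of the point. It does not remove it: a better estimator than the default exists at almost no cost, and chi-square also meets small expected counts.

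Three stronger readings are not supported:
- A reader might infer that few people will average 6000 steps. The 4000 figure describes Black adults generally, not this sample; no SD is given; HealthyCells+ pays a bonus at 6000 steps, and both arms set adaptable step goals. On the other side, enrolment is restricted to insufficiently active people and one arm gets no step incentive. The share cannot be settled from the article.
- A reader might infer that the categorical odds ratio will often be infinite. That holds only if roughly 9 to 13% reach the category (about 20 to 46% of trials), and only if a logistic model is used.
- A reader might infer that an inflated odds ratio will drive the next trial. The article names recruitment, retention and adherence as what is critical for planning it.

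**Conclusion.** The point holds as an inexpensive improvement. For the continuous model, maximum likelihood overstates a true log odds ratio of moderate size by about 8 to 14% on average, and Firth's method brings this to within about 2% (up to 3% if 27% are abstinent). This rests on the 20% and 75% targets being roughly met and on a near-normal step distribution. The effect is systematic but too small beside sampling error to change a reader's conclusion from one trial of this size.

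For the 6000-step split the risk is conditional on an unstated share: 2 to 12% of trials without a finite odds ratio at shares of 23 to 31%, and 34 to 46% at a share near 9%, with no true association. Under chi-square the matching problem is small expected counts. Nothing here is a contradiction in the article or an error that bears on the feasibility benchmarks.

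**What to change.** Add one sentence to the exploratory analyses: logistic models for abstinence will be fitted by Firth's penalised likelihood with profile-likelihood confidence intervals, an option in the logistic procedure of the SAS version already named. Keep continuous steps as the lead analysis. Report the 6000-step split as a 2x2 table of counts with a penalised odds ratio or an exact test, whichever model was intended. If an analysis plan already specifies this, no change is needed beyond making the article consistent with it.

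The cost is one option in the program and one sentence. The downside is that reported odds ratios become slightly smaller. Sample size, data collection and the feasibility criteria are unchanged.

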### Qualitative Analysis Plan

The baseline and exit interviews will be evaluated separately to comprehensively understand participants’ experiences and impressions at different stages of the mHealth intervention. Transcripts from both interviews will be analyzed in NVivo (version 12; Lumivero) using an inductive thematic approach [110,111]. A codebook will be developed collaboratively by coding a subset of interviews, with iterative refinements to ensure reliability before the lead author’s independent coding of the remaining transcripts. Periodic team reviews will resolve discrepancies.

The baseline interview will assess participants’ initial perspectives and familiarity with mHealth tools, which may inform their engagement with the intervention. Key focus areas will include motivation for participating in mHealth research, smartphone use habits, and previous experiences with health apps and Bluetooth-enabled devices. By examining these factors, the analysis will capture participants’ baseline comfort levels with digital health tools, previous exposure to apps for smoking cessation and physical activity, and any initial preferences for culturally tailored health behavior interventions within the Black population. Insights from these domains will provide context for interpreting participants’ engagement with the intervention and potential barriers that could influence adherence.

The exit interview will assess participants’ experiences with the intervention, focusing on perceptions of the cultural tailoring and usability of the intervention components. A central focus will be feedback on the e-book modeled after *Pathways to Freedom* [48], with analysis capturing participants’ impressions of its cultural relevance, clarity, and perceived impact on smoking cessation. Participants’ feedback on which sections resonated, any challenges encountered, and suggestions for improvement will provide insights into enhancing this culturally tailored component. Further domains in the exit interview will evaluate participants’ overall impressions of the app features, experiences with the smartwatch, adherence to NRT, and any technical issues encountered with study equipment. This analysis aims to identify strengths and weaknesses of the intervention from the user perspective, including insights into specific app features that supported or hindered engagement and practical challenges with using the devices.

We will synthesize findings from the baseline and exit interviews to identify overarching themes related to engagement, cultural resonance, and barriers to adherence. This holistic analysis will reveal how initial expectations and previous experiences influenced participant experiences and how the intervention can be refined to improve acceptability and effectiveness for larger-scale studies. Examining recurring themes across interviews may provide actionable insights for enhancing intervention design, especially regarding cultural tailoring, usability, and support for behavior change.

### Integration of Study Findings

We will use a mixed methods approach to capture a holistic view of intervention feasibility and participants’ experiences [112]. Quantitative data will provide intervention outcomes and milestones, and qualitative findings will uncover insights into participants’ expectations, experiences, and perceptions regarding the intervention. Triangulation will occur through a systematic comparison of quantitative metrics with qualitative themes [112,113]. For example, if quantitative results indicate high smoking cessation rates, qualitative data will be examined to identify participant-reported factors that facilitated this success. Conversely, if step count improvements are minimal, qualitative insights may help reveal barriers to physical activity engagement or limitations within the app that could be addressed in future studies. This combined approach will provide information about feasibility and generate participant-driven insights, increasing the likelihood that future interventions will be effective and tailored to meet community needs.

## Results

This study was reviewed and funded by the National Institute of Minority Health and Health Disparities (Multimedia Appendix 3). This study was approved by the institutional review board of the University of Oklahoma Health Sciences Center (protocol #14094) on 12/10/2021. Data collection is expected to start in February 2025 and finish in September 2025 (Figure 6 depicts the CONSORT [Consolidated Standards of Reporting Trials] diagram). Primary data are expected to be analyzed by October 2025. The preparation of manuscripts on primary and secondary outcomes is expected to start in late 2025 and early 2026.

**Figure 6 figure6:**
[figure not shown]
Participant recruitment, allocation, intervention adherence, and follow-up in the feasibility randomized controlled trial evaluating the HealthyCells interventions for smoking cessation and physical activity promotion (CONSORT [Consolidated Standards of Reporting Trials] flow diagram).

## Discussion

### Principal Findings

This study evaluates the feasibility of the HealthyCells intervention, an app-based mHealth approach integrating financial incentives for smoking cessation and physical activity promotion among Black adults. We anticipate that participants in the HealthyCells+ group, who receive incentives for both smoking abstinence and physical activity, will achieve greater increases in daily step counts and higher rates of CO-verified smoking abstinence compared to the HealthyCells group, who are incentivized for smoking abstinence only. Feasibility metrics, including recruitment, retention, and participant adherence, are expected to demonstrate strong engagement and acceptability of the intervention over the 9-week study period.

### Comparison to Prior Work

This study builds upon previous MHBC mHealth interventions, such as See Me Smoke-Free [114] and PhoS [115], which showed potential to promote behavior change but were limited by reliance on self-reported outcomes and low adherence rates [46,116,117]. In contrast, HealthyCells incorporates objective measures of behavior (eg, CO breath samples for smoking abstinence and step counts verified by smartwatches), addressing these limitations. In addition, culturally relevant content, such as that inspired by *Pathways to Freedom* [48,49], distinguishes HealthyCells from other interventions by tailoring messages to resonate specifically with Black adults. This study also advances CM research by combining financial incentives for multiple behaviors, a strategy that has shown promise in previous studies [34-38].

### Strengths and Limitations

A key strength of this study is its focus on a population disproportionately affected by tobacco- and obesity-related health disparities. By leveraging mHealth technology and CM, this intervention offers a scalable and accessible approach to behavior change. Objective tracking of outcomes ensures data reliability, and the inclusion of culturally tailored content enhances the potential for participant engagement.

However, this study has limitations inherent to feasibility trials. The sample size (n=60) is small and not powered to detect statistically significant differences in outcomes. In addition, the absence of a control group limits conclusions about the intervention’s effectiveness. Despite these limitations, this study will provide critical pilot data for a fully powered randomized controlled trial.

### Future Directions

Findings from this feasibility study will guide the refinement of the HealthyCells intervention for larger-scale trials. Future research will explore the effects of long-term interventions, the maintenance of behavior change after incentives are withdrawn, and the scalability of interventions to other underserved populations. In addition, further refinements to the app based on participant feedback will aim to enhance usability and engagement. Ultimately, this research has the potential to contribute to health equity by addressing smoking and physical inactivity in high-risk populations using innovative, culturally tailored, and technology-driven strategies.

## Appendix

Multimedia Appendix 1 Overview of study measures across each assessment type.

Multimedia Appendix 2 Overview of scheduled assessment and menu options available in both study apps.

Multimedia Appendix 3 National Institute of Health peer-review report.

## Abbreviations

CM: contingency management
CO: carbon monoxide
CONSORT: Consolidated Standards of Reporting Trials
MHBC: multiple health behavior change
mHealth: mobile health
NRT: nicotine replacement therapy
REDCap: Research Electronic Data Capture
